### Recruitment

Registered students at the University of Dublin, Trinity College, Dublin, will receive an email advertising the study and inviting students to take part. Interested students will be able to visit a website to receive more information on the study, what will be involved in participating, the treatment, and how to make contact and proceed with screening. On agreeing to participate, informed consent will be completed online and thereafter the baseline screening questionnaires.

### Randomization

Using computer algorithms to score screening instruments at baseline, participants will be automatically randomized to either the active intervention group or a waiting list control group. Participants will be immediately informed about the randomization outcome. The randomization procedure will be managed by a person independent of the research group.

### Interventions

#### Silver Cloud platform

Delivered through the SilverCloud platform, the program for the treatment of GAD employs several innovative engagement strategies for improving the user experience. These are divided into several categories: personal, interactive, supportive, and social.

#### Personal

The user has his or her own secure homepage, and can fill in a profile with basic information about themselves. As well as establishing a sense of ownership, this information is also useful for the supporter, allowing the supporter to provide more personal feedback. The homepage is intended to provide a reflective space; the user can document their thoughts and feelings, and these can be elaborated on within the journal application, which also acts as the vehicle for therapeutic writing exercises. The user has actions suggested to them, and as they complete modules of the program their achievements are noted. Users are free to access the modules in any order they wish, in either a linear or non-linear manner, contributing to a sense of empowerment. Alongside the central content, a range of satellite applications are provided, such as a goal-setting application which can be used independently of the program content. Applications are released as the user completes modules, with the intention of maintaining engagement by introducing new features over time and not overwhelming the user initially. Users can also control which applications appear on their home page.

#### Interactive

The program includes a number of interactive elements and graphical exercises which are aimed at engaging users with the therapeutic content, for example, reflecting on their own thinking style. Users also have the ability to respond to content, indicating whether they like it, and also to comment on it. Both exercises and comments can be explicitly shared with the supporter. The user is provided with immediate feedback wherever possible; for example, when a charting exercise such as a mood chart is completed, the application item is graphically updated on the home page. Likewise, items are ticked off on the to-do list when completed and achievements are unlocked in each module summary.

#### Supportive

Each user has an assigned supporter who provides weekly reviews of their progress on the program. This support is asynchronous, whereby the supporter sets a date to review their user’s progress, and they do not provide feedback, support or contact outside this time. The supporter can support multiple users, logging in once weekly for instance, and reviewing the work of all their online users within an allocated time period. Such asynchronous online contact may be logistically easier to implement for many services compared to motivational interviewing and telephone support. The system supports the exchange of messages between the user and supporter, but goes beyond email as the user is encouraged to share their content (such as completed exercises and comments) with their supporter. This shared content allows the supporter to respond in a more personal way and provide guidance as well as encouragement to keep using the program. Adherence information is also available to the supporter, and they can keep track of the user’s progress. This is all personally sensitive information, and so a shared view is provided in the user interface where they can see the supporter’s view of their data. By making the visibility of user data to the supporter more transparent, as well as the ability to explicitly change the sharing status of data, the user is provided with a greater sense of control while facilitating a meaningful interaction with the supporter.

#### Social

While group therapy and peer group support are well established, introducing contact with other users within any online system raises a number of ethical concerns regarding the possibility for unhelpful or negative content or communications. As a first step, the user can see anonymous indications of other people in the system. The intention is to reassure users that they are not alone in experiencing difficulties and that many other people have experienced similar problems and overcome them. Users can respond to content by indicating that they ‘like’ it, and can see how many other people liked it, helping to reduce the sense of isolation. Other more detailed shared content (such as tips and ideas) is subject to supporter moderation.

### Computerized cognitive-behavior therapy (cCBT) program

*Calming Anxiety* is a six-module online CBT-based intervention for GAD. The structure and content of the program modules follow evidence-based principles of CBT for GAD treatment based on the AMW model of GAD [27]. The treatment comprises cognitive, emotional, and behavioral components that include self-monitoring, relaxation training, self-control desensitization, gradual stimulus control, cognitive restructuring, and worry outcome monitoring [26]. The treatment is delivered on a Web 2.0 platform using media-rich interactive content. The content of each module is described briefly in Table 1 below. Each module is structured in an identical way and incorporates introductory quizzes, videos, informational content, interactive activities, as well as homework suggestions and summaries. In addition, personal stories and accounts from other clients are incorporated into the presentation of the material.

**Table 1 T1:** Calming anxiety: description of module content

**Module name**	**Brief description**
Getting Started	Outlines the basic premise of CBT and provides some information about anxiety. Users are encouraged to explore their current difficulties with anxiety and to begin monitoring their anxiety levels.
Understanding Moods and Emotions	This module describes the behavioral, physical, and emotional aspects of the Thoughts-Feelings-Behaviour (TFB) cycle. The user is introduced to relaxation practices. Users start to build their own anxiety-related TFB cycles
Anxious thoughts and worry	This module focuses on noticing anxious thoughts and worry, and ways of relating to these thoughts, including acceptance, distraction, and ‘worry time’.
Face your Anxiety, Step by Step	This module outlines why avoidance is harmful, and breaks down the steps needed for successful graded exposure. Users are encouraged to build their own fear hierarchies and to begin working through them.
Challenge your Anxious Thoughts	This module explains negative automatic thoughts, their role in anxiety, and how to challenge them. Users are encouraged to challenge the thoughts in their TFB cycles, and make use of helpful thoughts.
Bringing it all Together.	In this final module, users are encouraged to bring together all the skills and ideas they have gathered so far, note their personal warning signs, and make a plan for staying well.

### Waiting list control

Participants in the waiting list control group will not receive any treatment for the duration of the intervention for the immediate treatment group (six weeks). At week seven the waiting list participants will be given access to treatment under the same conditions as the immediate treatment group received (Figure 1).

**Figure 1 F1:**
[figure not shown]
Flowchart of the study CONSORT.

### Support during treatment

Each participant will be assigned a supporter who will monitor participant’s progress throughout the trial. Once a participant is assigned to the active treatment condition at their first login there will be a message from their supporter. This message welcomes them to the program, highlights aspects of the program, and encourages them in the use of the program. Each week the supporters will login and review participants progress, leaving feedback for them and responding to the work they have completed. Participating supporters will receive training in the program and how to deliver feedback.

Supporters will be graduate psychology students and will be qualified to at least masters level, some with doctorates. Each supporter will be assigned participants to provide post-session feedback of between 10 and 15 minutes per participant per session.

### Assessments

At baseline, assessments (see Table 2) including Sociodemographics & History Questionnaire, Generalized Anxiety Disorder-7 (GAD-7), Penn State Worry Questionnaire (PSWQ), Beck Depression Inventory (BDI-II), Work and Social Adjustment Scale (WSAS), and EuroQol (ED-Q5) will be completed for screening purposes. Thereafter the GAD-7, PSWQ, BDI-II, ED-Q5 and WSAS will be completed at the end of treatment, week six (for both the active treatment group and the waiting list participants). The active treatment group will complete GAD-7, PSWQ, BDI-II, ED-Q5 and WSAS at the first follow-up, week 12 (three months). After each session supporters will provide post-session feedback. Thereafter participants will be asked to complete the Helpful Aspects of Therapy Form (HAT). The measure Satisfaction with Treatment (SAT) will be administered at week six.

**Table 2 T2:** Study measures to be used

**Measure**	**Assessment**	**Time of assessment**
Generalized Anxiety Disorder-7 (GAD-7)	Anxiety symptoms	Baseline, post-treatment and follow-up
Sociodemographic & History Questionnaire	Gender, age, marital status, education, occupation, socioeconomic status, and history	Baseline
Penn State Worry Questionnaire (PSWQ)	Symptoms of anxious worry	Baseline, Post-treatment and follow-up
Beck Depression Inventory (BDI-II)	Depression symptoms	Baseline, post-treatment and follow-up
EuroQol (EQ-5D-5 L)	Quality of Life indicators	Baseline, post-treatment and follow-up
Work and Social Adjustment Scale (WSAS)	Work and Social Adjustment scale	Baseline, post-treatment and follow-up
Engagement and Usage data	Engagement and usage	Continuous
Satisfaction with Treatment (SAT)	Satisfaction with therapy	Post-treatment
Helpful and Hindering Aspects of Therapy (HAT)	Helpful and hindering aspects of therapy	After each session

### Measures

#### Primary outcome

The General Anxiety Disorder questionnaire (GAD-7) [67] comprises seven items measuring the symptoms and severity of GAD based on the DSM-IV diagnostic criteria for GAD. The GAD-7 has good internal consistency (0.89) and good convergent validity with other anxiety scales [68]. Increasing scores indicate a greater severity of symptoms [69]. Scores of 5, 10, and 15 are taken as the cutoff points for mild, moderate, and severe anxiety, respectively. The GAD-7 is increasingly used in large-scale studies as a generic measure of changes in anxiety symptomatology [37,70]. Using the threshold score of 10, the GAD-7 has a sensitivity of 89% and a specificity of 82% for GAD; it is considered congruent of DSM-IV as a clinical case for GAD [67].

#### Secondary outcomes

The Sociodemographic Information & History questionnaire is based on the History Questionnaire used in an earlier study [61]. It will be developed for the present study and will collect demographic details of the participants. It will collect data on any previous diagnosis of anxiety disorders and on the length of time that one experiences anxiety symptoms. It will collect data on participant’s experience of counseling and therapy, and medication for anxiety. The questionnaire will collect data on whether one has a previous diagnosis of an organic mental health disorder such as schizophrenia, psychosis, or bipolar disorder. In addition it contains items related to the comorbidity of anxiety with the presence of psychosis, alcohol and drug misuse, and/or any recent medical diagnosis.

The Penn State Worry Questionnaire (PSWQ) [66] consists of 16 items and is considered a valid clinical measure of the worry characteristic of GAD. Each item is measured on a 5-point Likert scale (1 - not at all typical of me to 5 - very typical of me) and a total score ranging between 0 and 80 is calculated by summing all items. Psychometric evaluations have revealed a high internal consistency (α = 0.86 to 0.95) and test-retest reliability over four weeks (*r* = 0.74 to 0.93) [71]. The measure is able to differentiate between patients with GAD and those with other anxiety disorders [72].

The 21-item Beck Depression Inventory - Second Edition (BDI-II) [73] is a widely used questionnaire developed for the assessment of depressive symptoms that correspond to the criteria for depressive disorder diagnosis as outlined in The American Psychiatric Associations Diagnostic and Statistical Manual of Mental Disorders - Fourth Edition (DSM-IV) [74]. Each item is scored on a scale from 0 to 3. The BDI-II manual states that a cutoff score of 17 has yielded a 93% specificity and 18% sensitivity for the presence of major depression (Beck *et al.*[73]). The scale designates levels of severity: minimal (0 to 13); mild (14–19); moderate (20 to 28); and severe (29 to 63) [73].

The BDI-II has been found to have an excellent internal consistency and test–retest reliability with a diverse range of samples [73,75,76]. The BDI-II has demonstrated a good convergent validity with other measures of depression among clinical and nonclinical adult samples [77].

The EuroQol 5D (EQ-5D) questionnaire [78] is a generic instrument of health-related quality of life. Part one records self-reported problems in each of five domains: mobility, self-care, usual activities, pain and/or discomfort and anxiety and/or depression. Each domain is divided into three levels of severity corresponding to no problems, some problems, and extreme problems, which allows a population-based preference score or societal index (SI) to be obtained. Part two records the subjects self-assessed health on a Visual Analogue Scale (VAS), a 10 cm vertical line on which the best and worst imaginable health states score 100 and 0, respectively.

The Work and Social Adjustment (WSA) questionnaire [79] is a simple, reliable, and valid measure of impaired functioning. It is a five-item self-report measure that provides an experiential impact of a disorder from the patient’s point of view. It looks at how the disorder impairs the patient’s ability to function day-to-day on five dimensions: work, social life, home life, private life, and close relationships.

### Other participant measures

The Helpful Aspects of Therapy Form (HAT) [80,81] is an instrument that assesses the most significant events in the therapy. Participants are asked to describe in their own words anything they engaged with in the session that was helpful or hindering for them.

The Satisfaction with Treatment (SAT) questionnaire [82] establishes a net promoter score that serves as a tool to gauge customer satisfaction. It includes one question: How likely is it that you would recommend this treatment to a friend or colleague? The measure also asks several other quantitative questions regarding satisfaction with accessing treatment online. The satisfaction measure contains two qualitative questions asking participants to describe what they most liked and least liked about the online treatment.

The pre-treatment and during treatment dropout questionnaires are two simple questionnaires, one asking about the reasons for deciding to dropout without beginning treatment and the second asking about the reasons for dropping out during treatment. The link for each of these will be contained in the appropriate emails that supporters send to their respective participants, following the protocol. Pre-treatment dropout: after one week the supporter can send the questionnaire by email. Participants discontinue treatment: after one missed session the supporter should send a reminder message to the participant by email. If after one further week the participant has not responded, the supporter can send the questionnaire asking about the reasons for dropout.

### Engagement and usage data

The online system will collect anonymized descriptive information relating to engagement and usage. Data collected will include the number of sessions completed, mean time spent on the program, average number of sessions per user, and average length of a session. A session is defined as an instance where a user logs onto the system. Session time estimation will always be an imperfect calculation, as users may be interrupted or take breaks within a session, and may not formally log out of the system. All client activity within the system such as reading content pages, saving a journal entry, or updating an activity, is logged with a time stamp. Starting with the log entry of the client logging on, the total time is calculated by adding up the time that elapses between each subsequent log record (in the same manner as popular web analytics software). On its own, this will yield a result vulnerable to overestimation of session time. To avoid counting periods where the user is not actively engaged with the system, any interactions taking longer than 30 minutes are counted as 1 minute. Any period of inactivity longer than three hours will start the count on a new session, rather than extending the time of the current session. Use of different program components will be measured. Data related to supporter reviews will be collected.

### Ethical considerations

Information made available to all prospective participants will inform them of exactly what is involved in participating, including the objectives of the trial and its importance. Participants will be informed of the importance of the waiting list control group. Informed consent will be obtained from each participant before randomization. Participants will know that their involvement is voluntary and they can withdraw their participation at any time without prejudice. Informed consent is collected online through participants digital signature and is returned online.

### Planned statistical analysis

The analyses will be based on the intention-to-treat principle, including those who began treatment and provided follow-up data irrespective of treatment compliance. Missing data will be handled using Last Observation Carried Forward (LOCF). Effects will be tested at the 0.05 level. Analysis of variance (ANOVA)will be used to investigate any baseline demographic or clinical differences between the groups.

To test the main hypotheses, repeated measures ANOVA will be performed for the primary outcome measure for anxiety (GAD-7). Thereafter ANOVAs will be executed for the BDI-II, PSWQ, EQ-5D and WSAS. Contrasts will be conducted comparing changes from baseline to post-treatment for each group separately. Further analysis of baseline demographic variables and any relation to outcomes will be conducted. Effect sizes (Cohen’s d) will be calculated both within and between groups, based on the pooled standard deviation. For Cohen's d an effect size of 0.2 to 0.3 can be considered a small effect, around 0.5 a medium effect, and 0.8 upwards a large effect [83].

Analysis will be made to determine the proportion of participants who make a clinically meaningful change at the end of treatment and at follow-up. Pre-treatment, post-treatment, and follow-up GAD-7, BDI-II and PSWQ scores will be compared with clinical cutoffs to provide an indicator of remission. Remission is defined as the number of participants who initially scored at or above the established clinical cutoffs, and then at post-treatment and follow-up scored below the established clinical cutoffs: GAD-7 total score <10 [67]; BDI-II total score <14 [84], PSWQ <45 [85], and WSAS <10 [79]. In addition, we will calculate the relative risk of anxiety and depression by dividing the event rate (anxiety or depression) post-treatment by the event rate pre-treatment [70]. An estimation of recovery will be made by identifying the number of participants in each group who demonstrated a reduction of 50% of pre-treatment GAD-7, BDI-II and PSWQ scores [70]. In addition we will also calculate the number of reliably changed and recovered participants using Jacobson and Truax’s [86] criteria.

HAT data will be analyzed qualitatively following the descriptive and interpretative framework described by Elliott and Timulak [87]. Participants’ responses will be considered within domains of helpful and non-helpful events and impacts. Firstly, individual units of text that could stand meaningfully out of their context will be identified. Next each of these will be organized into domains of helpful events and helpful impacts. Similar events and impacts will be grouped into categories, which will be then finalized and suitably named and defined. The process is organic, involving constant reference to the source data [88].

SAT data [82] will firstly establish the net promoter score. Descriptive statistics will be used to report on other quantitative questions, and qualitative data will be analyzed following the descriptive and interpretative framework described by Elliott and Timulak [87]. Similarly, data from dropout pre-treatment and during treatment will be analyzed qualitatively.

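### The set labelled intention-to-treat depends on two post-randomisation events, and one of them (starting treatment) can exclude participants from the active arm only

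*Protocol article*

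**What the plan says.** The protocol's Planned statistical analysis section defines the set in one sentence, which names the intention-to-treat principle and then continues "including those who began treatment and provided follow-up data irrespective of treatment compliance". The next sentence reads "Missing data will be handled using Last Observation Carried Forward (LOCF". No section says that everyone randomised is analysed in the assigned group.

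Four other parts of the protocol bear on this sentence:

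- **Randomization**: allocation is automatic once the baseline instruments are scored, so a student who is allocated to the programme and never opens it has already been randomised.
- **Waiting list control**: "Participants in the waiting list control group will not receive any treatment for the duration of the intervention", and then "At week seven the waiting list participants will be given access to treatment".
- **Assessments**: the outcome scales "will be completed at the end of treatment, week six (for both the active treatment group and the waiting list participants". The later assessment is described for one arm: "The active treatment group will complete GAD-7, PSWQ, BDI-II, ED-Q5 and WSAS at the first follow-up, week 12 (three months".
- **Other participant measures**: a separate questionnaire asks about "reasons for deciding to dropout without beginning treatment".

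**The concern.** An intention-to-treat set is fixed at randomisation. This sentence adds two filters that operate afterwards, and they do not act alike in the two arms. The filters govern all the analyses, including the repeated measures ANOVA of GAD-7 that tests the main hypothesis. If they are applied as written, the week-6 comparison is no longer between the two groups that randomisation formed, yet the result would be reported as intention-to-treat.

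**Working it through.** **Step 1. Apply each condition to each arm at week 6, the only point at which both arms are assessed.**

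| Condition | Active arm | Waiting list |
|---|---|---|
| Started treatment | Removes non-starters, even those who return week-6 scores | Cannot be met or failed by week 6; access opens at week 7 |
| Follow-up data, if this means week 6 | Removes non-responders | Removes non-responders |
| Follow-up data, if this means week 12 | Removes week-12 non-responders, even those with week-6 scores | No week-12 assessment is described |

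The starting condition is therefore one-sided on any workable reading. The data condition is two-sided only if it means week 6. Table 2 lists post-treatment and follow-up as separate occasions, which leans towards week 12, but the analysis section does not say.

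**Step 2. Set the data condition beside LOCF.** A student with only a baseline score is the main case in which LOCF would supply a week-6 GAD-7 value, and the data condition removes that student. What remains for LOCF is mostly a missing week 12 after an observed week 6, or one missing scale among several.

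**Step 3. Size of the one-sided exclusion.** The protocol gives no non-starter rate and no outcomes for non-starters, so all inputs here are assumed. Starters improve 5 GAD-7 points and the waiting list 2. A share p of the active arm never starts and improves m points. The control arm is kept whole.

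- All-randomised difference = (1 − p) × 5 + p × m − 2
- Difference in the set as written = 5 − 2 = 3.0
- Overstatement = 3.0 / (all-randomised difference) − 1

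| p | m | All-randomised difference | Overstatement |
|---|---|---|---|
| 0.10 | 2 | 4.5 + 0.2 − 2 = 2.7 | 3.0/2.7 − 1 = 11% |
| 0.10 | 1 | 4.5 + 0.1 − 2 = 2.6 | 3.0/2.6 − 1 = 15% |
| 0.20 | 2 | 4.0 + 0.4 − 2 = 2.4 | 3.0/2.4 − 1 = 25% |
| 0.20 | 1 | 4.0 + 0.2 − 2 = 2.2 | 3.0/2.2 − 1 = 36% |
| any | 5 | 3.0 | 0% |

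If m exceeds 5, the sign reverses and the set as written understates the effect.

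**Step 4. False-positive rate with no true effect.** The arm size of 50 comes from the Sample size section. It reproduces with a one-sided test: 2 × (1.645 + 0.842)² / 0.5² = 49.5, rounded up to 50. A two-sided test would need 2 × (1.960 + 0.842)² / 0.5² = 62.8, rounded up to 63. That is a separate matter; here 50 serves only as the arm size.

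Assume that a share e of the active arm is excluded, that those excluded do g SD worse than those kept, and that the waiting list stays at 50.

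- Bias = e × g (in SD)
- SE = √(1/[50(1 − e)] + 1/50)
- Two-sided error ≈ 1 − Φ(1.96 − bias/SE) + Φ(−1.96 − bias/SE)

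Results:

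- e = 0.10, g = 0.25: bias 0.025 SD, error about 5.2%
- e = 0.20, g = 0.50: bias 0.10 SD, SE √(1/40 + 1/50) = 0.212, error about 7.6%
- e = 0.40, g = 0.50: bias 0.20 SD, error about 13.9%

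**The case against.** The best defence is that the sentence means less than it seems to. The word used is *including*, which need not mean *restricted to*. The clause goes on to disregard compliance, and LOCF follows at once. On that reading the authors meant to keep non-compliers and fill in missing scores, and the fault is loose drafting. This reading is possible, but it is the less natural one: a plan to analyse everyone randomised would have no reason to name starting treatment and supplying data as the features of those included. Nor can an analysis plan that is not shown cure the sentence, because the protocol states a definition here and does not leave one open.

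Five stronger inferences are tempting, and the protocol does not support them:

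- *The control arm would be empty.* Receiving no treatment for six weeks is the control condition, so the starting condition simply has no meaning there. Emptying the arm is a strained reading.
- *LOCF has nothing left to impute.* It could still fill week-12 or single-scale gaps. The conflict concerns the primary week-6 outcome.
- *Non-responders are lost only from the active arm.* If follow-up means week 6, they are lost from both arms. Only the starting condition is specific to one arm.
- *This is a per-protocol set.* Participants who comply poorly but return data stay in, so it is a modified intention-to-treat set of starters with data.
- *The bias must favour the intervention.* The section on dropout from online treatments lists feeling better as well as poor clinical progress among reported reasons, so the direction is not established.

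**Conclusion.** The definition is wrong as written and should be corrected before analysis. The label and the inclusion rule conflict, and the starting condition acts on the active arm alone, on a group for which the protocol has a dedicated questionnaire. This much follows from the text without any assumption.

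The size does rest on assumptions. Across the scenarios with 10–20% non-starters who improve 1–2 points, the week-6 effect is overstated by about 11–36%. With 10–40% of the active arm excluded and a gap of 0.25–0.50 SD, a nominal 5% two-sided test has an error of about 5.2–13.9% under no true effect. Both are ranges over assumed inputs, not estimates for this trial, and both shrink to nothing if the excluded students fare as the others do.

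**What to change.** Replace the sentence with:

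> The primary analysis includes all randomised participants in the group to which they were randomised, whether or not they began treatment or provided post-baseline data; missing week-6 outcomes are handled by the primary missing-data method.

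Keep the present set only as a sensitivity analysis, labelled modified intention-to-treat (starters with data) and not per-protocol. State there whether the data required are from week 6 or week 12, and that the starting condition applies to the active arm only.

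The cost is wording. Baseline scores are collected before allocation, so they exist for everyone randomised, and the Trial status section describes a second recruitment round just beginning.

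There are two downsides. The headline effect may become less favourable. And the result for the added participants without week-6 data will depend on the missing-data method: under LOCF their change is set to zero. If none of the non-starters in the illustration returned week-6 data, the estimate would be 0.9 × 5 − 2 = 2.5 at 10% and 0.8 × 5 − 2 = 2.0 at 20%, below the all-randomised values of 2.6–2.7 and 2.2–2.4. The new set restores the randomised comparison, but it does not by itself recover the true effect.
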